**Fig. 1 fig1:**
[figure not shown]
Experiment Design (example of a rehabilitation period of 8–10 weeks). *Note*: Timeline from inclusion to study completion, depicting the cross-over design and the most common range of durations of experimental and control periods.

### Study population

2.3

Twenty adults (≥18 years of age) with supratentorial stroke admitted to the stroke unit of the Leo Polak Rehabilitation Centre in Amsterdam, will be recruited within the subacute phase (2 weeks - 6 months after the incident).

#### Sample size calculation/power analysis

2.3.1

In a previous study, 40 stroke patients in the sub-acute phase were allocated to either 20 30-min sessions of music-supported therapy (N = 20; 4 withdrew/excluded; 16 in final analysis) or twenty additional sessions of conventional therapy (N = 20; 2 withdrew/excluded; 18 in final analysis) [35]. The study found a significant correlation (r = 0.562, p = 0.024) between patients’ intrinsic motivation to engage in musical activities as measured by the Barcelona Music Reward Questionnaire (BMRQ, [36]) at baseline and improvement of upper-limb function as measured by the Action Research Arm Test (ARAT, [37]) at 3 months, which was not found in the comparator of occupational/physical therapy (r = −0.305, p < 0.21), with a significant difference between correlations (z = 2.4, p < 0.05). Using Gpower 3 analysis, we estimated that 18 participants are needed to observe a similar effect size for a sufficiently powered study (α = 0.05 and (1-β) = 0.8; ρ H1 = 0.56). This indicates that 20 participants completing the entire protocol would be required to observe an effect of motivation in music therapy, with a hypothesised attrition/missing data rate of 10–20 %. This sample size is similar to the number of participants used in studies showing an effect for our secondary objectives, ranging from 14 to 20 participants, on the effects of music therapy on motor function [38], cognition, and psychological wellbeing [39]. Recruitment will continue until 20 participants have completed the protocol.

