## Abstract

Stroke is a highly disabling condition, for which music therapy is regularly used in rehabilitation. One possible mechanism for the effects of music therapy is the motivational aspect of music, for example regarding treatment adherence based on improved mood. In this study, changes in motivation related to Neurologic Music Therapy (NMT) techniques during rehabilitation in the subacute phase after stroke will be investigated. Using a randomised within-subjects cross-over design, the effects of two NMT techniques and related motivational indices will be investigated. Data will be collected at three timepoints: baseline (TP1), after being randomised into groups and receiving NMT or standard care (TP2), and then at a third time point after the cross-over and having received both conditions (TP3). This design allows to counteract order effects, time effects due to spontaneous and/or nonlinear recovery, as well as single-subject comparisons in a relatively heterogeneous sample. Twenty adult participants who have experienced a supratentorial ischaemic or haemorrhagic stroke and are experiencing upper-limb impairments and/or cognitive deficits will be included. Behavioural measures of motor function, cognition, and quality of life will be collected, along with self-reported indices of overall motivation. The study outcomes will have implications for the understanding of the underlying mechanisms of music therapy in stroke recovery, more specifically regarding the relevance of motivational states in neurorehabilitation.

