### Statistical analysis

2.6

Descriptive statistics for all relevant variables, such as changes in motivation, upper limb function and/or attention/concentration skills, will be calculated (means, standard deviations, etc.). Assumptions of all statistical analyses will be checked, and appropriate measures will be taken in case of violations (e.g., transformations, nonparametric testing, or bootstrapping). Effect sizes will be calculated for each effect (e.g., Cohen's *d*). Statistical tests will be performed with an alpha level of p ≤ .05 to determine statistical significance of results. Because of the randomised design, possible bias introduced by missing data will be controlled for using an intention-to-treat (ITT) analysis performed on all subjects who complete the baseline measurements, to assess whether data is missing randomly. If so, these may be completed with imputed data. Given the relatively small sample size of the study, this allows for a per-protocol analysis to also be conducted on datasets with missing data points, and the results from the ITT analysis will be verified on subjects who completed the entire study protocol, including all measurements (e.g. Ref. [57]). If needed, data analysis procedures with more robustness for missing data will be utilised (i.e., multilevel models). The self-reported motivation for sessions attended for other interventions offered at the rehabilitation centre will be recorded and compared between subjects as well as between sequences (AB/BA). Carry-over effects due to the cross-over design will be assessed by examining a treatment-by-period interaction. A significant difference between the two intervention or control phases of the AB/BA sequence, will result in significant treatment-by-period interaction indicating a carry-over effect (Lim & In, 2021). In case a significant carry-over effect is found, we will control for this in the analysis.

Other aspects that may be used as covariates in post-hoc analyses to interpret results at the group level are individual differences in diagnostic intake measures, age, and qualitative clinical observations or situations that may affect motivational states.

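### The stated requirement of 18 participants holds only for an undeclared one-sided test; a two-sided 0.05 test needs 22, the planned 20 completers give 76% power, and the 20 is not defined consistently.

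*Protocol article*

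**What the plan says.** Section 2.3.1 starts from an earlier music-supported therapy study with 16 patients in the final analysis of the music arm. It cites this result: "The study found a significant correlation (r = 0.562, p = 0.024". From that it sets the inputs "α = 0.05 and (1-β) = 0.8; ρ H1 = 0.56" and concludes that "we estimated that 18 participants are needed to observe a similar effect size for a sufficiently powered study". Neither the sentence nor its inputs say whether the test is one- or two-sided.

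The section then moves from 18 to 20: "This indicates that 20 participants completing the entire protocol would be required to observe an effect of motivation in music therapy", and the same sentence goes on "with a hypothesised attrition/missing data rate of" 10–20%. It closes with a stopping rule: "Recruitment will continue until 20 participants have completed the protocol".

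Section 2.6 covers significance for the whole trial: "Statistical tests will be performed with an alpha level of" p ≤ .05, again with no direction.

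Elsewhere the 20 has another meaning. The Abstract says "Twenty adult participants who have experienced a supratentorial ischaemic or haemorrhagic stroke" and the stated deficits are to be included, and section 2.3 says that twenty adults are to be recruited.

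**The concern.** A reader who sees alpha 0.05 with no direction will take the test as two-sided, and on that reading the printed inputs do not give 18. This is the only power calculation in the article. If it was run one-sided and the test is then done two-sided, the trial has less power for this correlation than it reports.

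The second issue is what 20 counts. An attrition rate serves to turn completers into a number to enrol. In section 2.3.1 it accompanies the step from 18 to 20, yet the result is called a number of completers, while the Abstract and section 2.3 use the same figure for patients included or recruited. A reader cannot tell how many patients the trial expects to randomise.

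**Working it through.** **Inputs (section 2.3.1).** ρ under the alternative 0.56; α = 0.05; power 0.80; source r = 0.562 with p = 0.024 and n = 16; loss 10–20%. The null correlation is taken as 0, which is an assumption because the section does not state it.

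**Step 1: reproduce the 18.** Reject when r exceeds r_c = t / √(n − 2 + t²), where t is the critical value on n − 2 degrees of freedom. Power is the area beyond r_c under the exact bivariate-normal density of r at ρ = 0.56 (both tails for a two-sided test). At n = 18:
- One-sided: t = 1.746, so r_c = 1.746/√(16 + 3.05) = 0.400.
- Two-sided: t = 2.120, so r_c = 2.120/√(16 + 4.49) = 0.468.

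| Analysed n | One-sided power | Two-sided power |
|---|---|---|
| 17 | 79.2% | 68.5% |
| 18 | 81.4% | 71.4% |
| 20 | 85.3% | 76.4% |
| 21 | 86.9% | 78.7% |
| 22 | 88.3% | 80.7% |

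The smallest n reaching 80% is 18 one-sided, which is the printed figure, and 22 two-sided. Using 0.562 in place of 0.56 changes neither number.

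**Step 2: other methods.**
- Fisher z: n = ((z_α + z_power)/atanh ρ)² + 3, with atanh 0.56 = 0.633. One-sided: ((1.645 + 0.842)/0.633)² + 3 = 18.4, so 19. Two-sided: ((1.960 + 0.842)/0.633)² + 3 = 22.6, so 23. Two-sided power is 68.8% at 18 and 74.2% at 20.
- Noncentral t with a fixed regressor: 16 one-sided and 20 two-sided. Two-sided power is 76.8% at 18 and 81.6% at 20.

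No two-sided method reaches 80% at 18.

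**Step 3: sidedness of the source result.** t = 0.562 × √(14/(1 − 0.562²)) = 2.54 on 14 degrees of freedom, so two-sided p = 0.0235. This matches the printed 0.024; a one-sided p would be half of that.

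**Step 4: attrition.**
- If 20 is 18 inflated for loss: 18/0.9 = 20.0 and 18/0.8 = 22.5, so 20 to 23 enrolled.
- If 20 is the number of completers, as the stopping rule says: 20/0.9 = 22.2 and 20/0.8 = 25, so about 23 to 25 randomised.

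Under the stopping rule the attrition rate plays no part in obtaining 20. It bears only on how many must be randomised to reach 20.

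**The case against.** The strongest reply is that 18 is not an arithmetic error. It reproduces exactly as a one-sided result, the hypotheses in the Introduction are largely directional, and the article never claims a two-sided test. A condensed article may also leave sidedness to the full protocol, the analysis plan or the preregistration mentioned in section 2.5.3. This stands in part: 18 is correct for a one-sided test, and silence on sidedness would not by itself be a finding. But the article prints the calculation with its inputs, and those inputs under the usual two-sided convention do not give the printed answer. A directional hypothesis does not declare a one-sided test.

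It can also be said that the noncentral-t version gives 81.6% two-sided at 20. That is correct, but this version treats one variable as fixed, and it gives 76.8% at the 18 that the section derives.

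A reader might infer that 20 fails to cover 20% attrition and that only 16 patients would be analysed, with 65% two-sided power. The documents do not support this. Section 2.3.1 defines 20 as completers and recruits until 20 have completed, so dropouts are replaced. That figure would apply only if 20 were the number enrolled without replacement.

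Finally, the calculation concerns a correlation, whereas the primary analysis in section 2.6 is the BMQ-S change between periods. Correcting the figure says nothing about power for that comparison. This is true, and it limits the reach of the point.

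**Conclusion.** The point holds in a limited form. The printed 18 is right for a one-sided exact correlation test at ρ = 0.56 and wrong for a two-sided one, which needs 22. With the planned 20 completers, two-sided power is 76.4%, about 4 points short of 80%; one-sided it is 85.3% and the target is met. So it cannot be said outright that 80% power is not delivered: that depends on a sidedness the article does not state. These figures assume a null correlation of 0, bivariate normality, a true correlation of 0.56 and 20 analysable completers.

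The use of 20 for completers in section 2.3.1 and for patients included or recruited in the Abstract and section 2.3 is a real inconsistency. The stopping rule settles what is intended, so this is a matter of aligning the text and not a shortfall in analysed patients.

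**What to change.** In section 2.3.1, choose one of two statements:
- Two-sided: 20 completers give 76% power at ρ = 0.56 with α = 0.05, and 80% would need 22.
- One-sided: say that the calculation is one-sided, and in section 2.6 declare the matching correlation test one-sided with its expected sign. Twenty completers then give 85%. The sign needs stating because higher BMQ-S scores mean greater difficulty with motivation (section 2.5.1).

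Then define 20 once as the number completing the protocol, and use that definition in the Abstract and sections 2.3 and 2.3.1. Remove the attrition rate from the derivation of 20, and state instead that 10–20% loss implies about 23–25 randomised.

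The cost is wording and, under the two-sided option, a slightly less favourable power figure. The target of 20 completers does not change.

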#### Inclusion criteria

2.3.2

In order to be eligible to participate in the study, a participant should be above 18 years of age and have had their first-ever supratentorial stroke between 2 weeks and up to 6 months before enrolment. Moreover, participants will have a referral for a paretic upper limb, i.e., partial loss of the capacity to carry out a voluntary upper limb movement and/or difficulty with attention/concentration (e.g., complaints of being easily distractible, or unable to focus on a specific task in the presence of competing information, or decline in attention). Participants must be able to receive music therapy for a minimum of 2–3 sessions per week, aiming for a total of 9 sessions over a minimum of three weeks, reducing this to 6 sessions in 2 weeks if required. The frequency of sessions is based on the individual's ability and expected length of stay. Good command of the Dutch or English language is also a prerequisite for participation.

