### Treatment of subjects

2.4

The following two protocolised NMT techniques targeting motor recovery and attention training [8], will be used: Therapeutic Instrumental Music Performance (TIMP) and Musical Attention Control Training (MACT). Depending on the rehabilitation goals, namely upper limb recovery, increase of attention/concentration, or both, one or both methods are utilised during a music therapy session.

Therapeutic Instrumental Music Performance (TIMP) is a technique that utilises musical instruments to help patients to exercise impaired motor function and regain functional patterns of movement. TIMP musical exercises are designed to target specific movement patterns (such as pinching, grasping or a gross motor arm movement), with maximum repetition. TIMP involves the planning of functional exercises using musical instrument playing to meet functional physical goals, set within the multidisciplinary team, with the aim of transferring the therapeutic learning into real-world applications. The tactile and auditory feedback from playing musical instruments as a part of a structured program of upper limb rehabilitation following stroke create so-called audio-motor coupling [42], thought to facilitate learning. During each session clients will perform clear rhythmical patterns using the affected upper limb, while the music therapist accompanies them with a harmonic musical instrument (e.g. piano or guitar) adjusted at the beginning of each session according to the state and progress of each client [43]. The duration of each NMT session will be 30 min. Musical Attention Control Training (MACT) is a technique that provides structured active or receptive musical exercises involving precomposed performance or improvisation, in which musical elements cue different musical responses, to practise specific attention functions, namely: sustained, selective attention, inhibition/switching, and turn-taking [44]. When linked with non-musical information, music adds structure and organisation, emotion, and appeal to the information in order to increase the probability that attention will be focused, maintained and/or switched [8]. The benefits of the neurologic music therapy protocols used in this study (TIMP and MACT) in particular for stroke survivors have been previously reported [[45], [46], [47]] although the evidence is limited and, arguably, not well established.

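### The stated 80% power is for a correlation with arm-function gain, and holds only one-sided and only if at least 18 of the 20 completers have an arm deficit

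*Protocol article*

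**What the plan says.** All references are to the protocol article.

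- **Source of the size (2.3.1).** In the music arm of a previous stroke study, with 16 patients analysed, baseline BMRQ score showed a "significant correlation (r = 0.562, p = 0.024") with "improvement of upper-limb function as measured by the Action Research Arm Test".
- **The size (2.3.1).** With alpha 0.05, power 0.8 and rho 0.56, "we estimated that 18 participants are needed to observe a similar effect size for a sufficiently powered study". Sidedness is not stated. Then: "This indicates that 20 participants completing the entire protocol would be required", "with a hypothesised attrition/missing data rate of" 10–20%.
- **Closing rule (2.3.1).** "Recruitment will continue until 20 participants have completed the protocol". No number with an arm deficit is set.
- **Eligibility (2.3.2).** Referral for "partial loss of the capacity to carry out a voluntary upper limb movement and/or difficulty with attention/concentration", so a patient referred for attention alone qualifies.
- **Treatment (2.4 and 2.2).** Section 2.4 says: "Depending on the rehabilitation goals, namely upper limb recovery, increase of attention/concentration, or both, one or both methods are utilised". Section 2.2 says that every subject receives both techniques. These two statements do not agree and must be reconciled.
- **Analyses (2.6).** The primary analysis compares BMQ-S change between the control and intervention periods. Correlations of motivation change with motor, cognitive and mood change come in addition. Correlations of musical engagement with functional improvement are exploratory.

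**The concern.** The planning correlation describes how music reward relates to recovery of the arm. The count of 18 carries over to this trial only for patients whose arm function has room to recover. Eligibility and the closing rule, however, count every completer alike, including those referred for attention only. If several of the 20 are of that kind, a motivation–ARAT correlation rests on fewer than 18 informative patients, or on 20 patients in whom 0.56 need not hold.

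At stake is how a null result is read. The motivation–function correlation is a stated hypothesis (Introduction), and the article says that the size is enough to observe an effect of motivation in music therapy. A reader who trusts the 80% could take a non-significant ARAT correlation as evidence against the mechanism, although the test had much less power than stated.

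**Working it through.** **Inputs.** From 2.3.1: rho = 0.56, alpha = 0.05, power 0.80, 18 participants, 20 completers. Not in the documents: sidedness, and the share f of completers with an arm deficit. Both are varied below.

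**Source check.** With r = 0.562 and n = 16, t = r√(n−2)/√(1−r²) = 2.54 on 14 df, two-sided p = 0.023. This is close to the stated 0.024, so the source figures are coherent and the source test was two-sided.

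**Step 1: reproduce 18.** Test one Pearson correlation against 0 under bivariate normality. The critical value is r_c = t/√(t² + n − 2), with t the 0.95 quantile (one-sided) or 0.975 quantile (two-sided) on n − 2 df. Power is the probability that r exceeds r_c under its exact distribution at rho = 0.56 (plus the lower tail if two-sided).

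For n = 18, one-sided: t = 1.746, r_c = 1.746/√(3.05 + 16) = 0.400, power 81.4%. For n = 17, power is 79.2%. So 18 is the smallest adequate n.

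| Method | One-sided n | Two-sided n |
|---|---|---|
| Exact | 18 | 22 |
| Fisher z | 19 | 23 |
| Point-biserial (noncentral t) | 16 | 20 |

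Only the exact one-sided test gives 18. The point-biserial model is for a fixed predictor, not for two measured scores.

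**Step 2: attrition.** 18/(1 − 0.10) = 20, and 18/(1 − 0.20) = 22.5, so 23. Because 20 is fixed as a number of completers, the margin is 20 − 18 = 2. It covers at most two completers without an arm deficit, and only if no other data are missing.

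**Step 3: exact power by number of completers with an arm deficit** (rho = 0.56, complete data).

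| Arm patients among 20 | One-sided | Two-sided |
|---|---|---|
| 20 | 85.3% | 76.4% |
| 18 | 81.4% | 71.4% |
| 17 | 79.2% | 68.5% |
| 16 | 76.8% | 65.4% |
| 14 | 71.0% | 58.5% |
| 12 | 64.0% | 50.6% |
| 10 | 55.6% | 41.7% |

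**Step 4: how secure is 18?** If each completer has an arm deficit with probability f, the chance that at least 18 of 20 do is binomial: 92.5% at f = 0.95, 67.7% at 0.90, 20.6% at 0.80, 3.5% at 0.70.

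**Step 5: does giving the ARAT to everyone help?** Simulate 20 completers, with rho = 0.56 among arm patients and zero ARAT change in the rest (an assumption), and test all 20 one-sided.

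| Arm patients | Mean gain of arm patients 0 SD | Mean gain 1 SD |
|---|---|---|
| 16 | 76% | 67% |
| 14 | 70% | 57% |

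The 80% is not restored. A mean gain that is unrelated to motivation adds spread between the two kinds of patient and lowers the correlation further.

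**The case against.** The strongest reply is that the sized correlation is not the primary analysis. Section 2.6 makes the BMQ-S contrast primary, every completer contributes to it whatever the referral, and the closest match to BMRQ with ARAT gain is only exploratory. On this view 0.56 is merely a borrowed planning value. The description of section 2.6 is right, and it limits the point: nothing here shows that the primary comparison is underpowered, and a reader should not infer that. But the article prints an 80% figure derived from a motivation–ARAT correlation, and it plans a correlation of motivation change with motor change. The conditions of that figure should be stated.

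Other stronger readings are tempting and are not supported:

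- **That attention-only patients cannot inform the correlation.** Section 2.5.1 does not restrict the ARAT to arm referrals, the Introduction notes that motor and cognitive symptoms often occur together, and section 2.2 has all subjects receiving both techniques. Such patients may be measured and may have some arm deficit. Little ARAT change in them is an assumption.
- **That the analysed number will fall below 18.** This happens only with three or more completers without an arm deficit, or with missing data. The mix is not given.
- **That 18 is miscalculated.** It reproduces exactly on a one-sided test.

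It is also fair that an analysis plan, not shown here, may define the set for each domain. Restricting the ARAT correlation to arm patients would be sensible, but it would not bring their number to 18.

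**Conclusion.** The point holds as a conditional one. The stated 80% applies to a motivation–ARAT correlation only if the test is one-sided and at least 18 of the 20 completers have an arm deficit and complete data. Neither eligibility nor the closing rule secures that number. Two-sided, 80% is missed even with all 20 (76%).

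The size of the shortfall depends on a mix that the documents do not give. One-sided, it is negligible at 17 arm patients (79%), moderate at 14 (71%) and large at 10 (56%). With 18 to 20 arm patients the one-sided figure stands (81–85%).

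The result assumes bivariate normality, a true rho of 0.56 in arm patients, and, where all 20 are tested together, little ARAT change in the others. It also takes for granted that a value observed with baseline BMRQ carries over to the motivation measure used. The finding concerns the reported power of one supporting correlation. It is not an error in the primary analysis.

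**What to change.** In section 2.3.1:

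1. State that the 80% refers to a one-sided test of a motivation–ARAT correlation in at least 18 completers with a paretic arm at baseline.
2. Replace the single figure with the power over the expected number of such completers, as in Step 3. If the test will be two-sided, give the two-sided column.
3. Drop the claim of sufficient power for that correlation where the expected number is below 18.
4. State that this figure does not apply to the primary BMQ-S comparison in section 2.6.

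Sections 2.2 and 2.4 should also be reconciled on whether every subject receives both techniques.

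The cost is a few sentences and a less favourable stated power. No extra patients, measurements or analyses are needed.

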The primary analysis concerns the change in motivation scores (BMQ-S) between the control and intervention period, controlling for the order of conditions. Additionally, a correlation between changes in motivation with changes in functional outcome measures (motor, cognition, mood) will be calculated. For our secondary analysis, changes in functional measures will be compared between control and intervention periods to assess effectiveness of NMT. As exploratory analyses, correlations between functional improvements and possible predictors such as musical engagement, optimism, personality traits and expectations of NMT will be calculated. Finally, self-reported motivation for other rehabilitation specialisms will be compared between the intervention and control period. Participants will be included if they have completed at least 6 sessions of Music Therapy.

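### The 80% power claim rests on a trait–function correlation, so the primary BMQ-S comparison has no stated power basis

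*Protocol article*

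**What the plan says.** Section 2.3.1 (Sample size calculation/power analysis) starts from an earlier parallel-group study. In its music arm (16 analysed, 20 sessions planned) the predictor was intrinsic motivation for musical activity "as measured by the Barcelona Music Reward Questionnaire (BMRQ, [36]) at baseline", and the outcome was "improvement of upper-limb function as measured by the Action Research Arm Test (ARAT, [37]) at 3 months". The correlation was 0.562. The protocol then says "Using Gpower 3 analysis, we estimated that 18 participants are needed to observe a similar effect size for a sufficiently powered study", with the settings "α = 0.05 and (1-β) = 0.8; ρ H1 = 0.56". From this it infers: "This indicates that 20 participants completing the entire protocol would be required to observe an effect of motivation in music therapy".

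Section 2.6 (Statistical analysis) defines a different main test: "The primary analysis concerns the change in motivation scores (BMQ-S) between the control and intervention period", with adjustment for the order of conditions. Relating functional gains to musical engagement comes later and has a lower status: "As exploratory analyses, correlations between functional improvements and possible predictors such as musical engagement".

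Section 2.5.1 (Study parameters) makes the BMQ-S the state-level motivation measure, treats the BMRQ as a trait measure of engagement with music, and lists the ARAT among the secondary outcomes.

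**The concern.** The calculation and the primary test share no variable and no type of statistic. One is a between-person correlation of a baseline trait with a motor gain. The other is a within-person mean difference on a state motivation questionnaire. The article nevertheless moves from the first to a statement about detecting a motivational effect in general.

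A reader will attach the 80%, and the description of the study as sufficiently powered, to the BMQ-S result. If that result is null, it could be taken as evidence against motivation as the mechanism of NMT, when the trial may have had little chance of detecting a moderate difference.

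**Working it through.** **1. Inputs from the article.** Section 2.3.1: alpha 0.05, power 0.80, correlation 0.56, stated n = 18, target of 20 completers, attrition or missing data 10–20%. Section 2.6: primary contrast on BMQ-S, adjusted for order; alpha 0.05, sidedness not stated. The article gives no BMQ-S difference, SD or correlation between time points.

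**2. Reproducing the stated 18.** Test of zero correlation, true value 0.56:

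| Method | One-sided 5% | Two-sided 5% |
|---|---|---|
| Fisher z: ((z_α + z_β)/atanh 0.56)² + 3 | 18.4 | 22.6 |
| Exact bivariate normal, power at n = 17 | 79.2% | 68.5% |
| Exact, power at n = 18 | 81.4% | 71.4% |
| Exact, power at n = 20 | 85.3% | 76.4% |
| Exact, smallest n for 80% | 18 | 22 |

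The 18 is therefore correct for this correlation if the test is one-sided, which the article does not say.

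**3. Does the 18 carry over to the primary test?**

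| | Calculation in 2.3.1 | Primary analysis in 2.6 |
|---|---|---|
| Motivation measure | BMRQ, trait, baseline only | BMQ-S, state, three time points |
| Other variable | ARAT improvement at 3 months | none; contrast of periods |
| Statistic | between-person correlation | within-person mean difference |
| Music sessions | 20 | target 9, minimum 6 |

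Power for the primary test depends on d_z = (mean within-person difference)/(SD of that difference). The BMRQ–ARAT correlation determines neither quantity.

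**4. What 20 completers can detect on the primary test.** For an AB/BA contrast adjusted for sequence, the test statistic is noncentral t with n − 2 degrees of freedom and noncentrality d_z·√n. At n = 20 this is 18 degrees of freedom. Two-sided 5% is assumed.

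- Smallest d_z for 80% power: 0.662 at n = 20. At n = 18 and 16 (20 reduced by the stated 10% and 20%) it is 0.703 and 0.753.
- Check at n = 20: noncentrality = 0.662 × √20 = 2.96.

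| Assumed d_z | Power at n = 20 | n for 80% power |
|---|---|---|
| 0.3 | 24.5% | 90 |
| 0.4 | 39.5% | 52 |
| 0.5 | 56.2% | 34 |
| 0.6 | 71.8% | 24 |
| 0.7 | 84.1% | 19 |
| 0.8 | 92.2% | 15 |

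If the test were one-sided, the smallest d_z at n = 20 would be 0.578, and power at d_z = 0.5 would be 69%.

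**5. The same difference in between-patient SDs.** Section 2.5.1 describes a comparison of changes, so each person's contrast is, up to sign, (TP3 − TP2) − (TP2 − TP1) = TP3 − 2·TP2 + TP1. With equal variance σ² and a common correlation ρ between time points, its variance is σ²(1 + 4 + 1) + 2ρσ²(−2 − 2 + 1) = 6σ²(1 − ρ). The detectable difference is then 0.662·√(6(1 − ρ)) SDs:

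- ρ = 0.6: 0.662 × √2.4 = 1.03
- ρ = 0.7: 0.662 × √1.8 = 0.89
- ρ = 0.8: 0.662 × √1.2 = 0.73

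The values of ρ are assumptions.

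**The case against.** The strongest reply is that a motivation–function correlation is not peripheral here. Section 2.1 frames motivation as a mechanism, and section 2.6 adds, directly after the primary comparison, a correlation of motivation change with functional change. The 0.56 could be a loose proxy for that. This softens the point but does not answer it: the added correlation uses BMQ-S change rather than a baseline BMRQ score, and it is not the primary comparison.

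Three further points have some force:

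- The SD conversion depends on how the contrast is read. If it meant the end of NMT against the end of control, the variance would be 2σ²(1 − ρ), and d_z = 0.662 would equal 0.59 to 0.42 SDs for ρ = 0.6 to 0.8. Section 2.5.1 favours the comparison of changes, but the SD figures remain conditional.
- Recruitment is to continue until 20 have completed, so n = 20 is the main case. The rows for 18 and 16 matter only if BMQ-S data are missing at the article's own 10–20% rate.
- Nothing here shows that 20 is too few, and the Discussion already calls the study relatively small. That remark does not withdraw the claim of sufficient power in section 2.3.1.

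It could also be said that an article leaves detail to a fuller document. But this is not an omission: the article states a calculation and draws a conclusion from it that does not follow.

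**Conclusion.** The concern holds. The only power figure in the article belongs to a BMRQ–ARAT correlation whose nearest planned counterpart is exploratory. The primary BMQ-S contrast has no stated effect size, SD or power.

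On a two-sided 5% test with 20 completers, the primary contrast has 80% power only if d_z is about 0.66 or more; at d_z = 0.5 it has 56%, and at 0.3 it has 25%. Under the comparison-of-changes reading, with assumed time-point correlations of 0.6 to 0.8, 0.66 corresponds to about 1.03 to 0.73 between-patient SDs of BMQ-S. The d_z values, the correlations and the two-sided test are assumptions, because the article gives none of them. The mismatch itself depends on none of these assumptions.

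**What to change.** In section 2.3.1, replace the concluding power statement with one for the primary test, for example: *With 20 completers, the order-adjusted within-person BMQ-S contrast has 80% power (two-sided 5%) for a standardised difference d_z of 0.66.* Then:

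- Convert this to BMQ-S points with a stated SD and its source. The sponsor must supply the SD, as the article has none.
- Say whether a difference of that size is plausible. If this cannot be supported, call the sample size pragmatic and present 0.66 as its sensitivity.
- Relabel the 0.56 calculation as applying only to the exploratory BMRQ–ARAT correlation, and state that 18 is a one-sided figure (81% power one-sided, 71% two-sided).

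Keep N at 20. The cost is wording only: no extra patients and no change to design or analysis. The stated sensitivity becomes less favourable.
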